# Viral load-guided immunosuppression after lung transplantation (VIGILung)—study protocol for a randomized controlled trial

**DOI:** 10.1186/s13063-020-04985-w

**Published:** 2021-01-11

**Keywords:** Lung transplantation, Immunosuppression, Graft rejection, Kidney failure, Torque teno virus, Randomized controlled trial

## Abstract

**Background:**

Immunosuppression including high-dose calcineurin inhibitors (CNI) is essential after lung transplantation. Dosing is usually guided by therapeutic drug monitoring adjusted to target trough levels of CNIs to keep the balance between over-dose causing severe toxicity and increased risk of infections or under-dose with a risk of graft injury. Adaptation of CNI-based immunosuppression by monitoring of torque teno virus (TTV), a latent nonpathogenic DNA virus, measured in the whole blood in addition to conventional therapeutic drug monitoring may reduce the toxicity of immunosuppression with similar efficacy.

**Methods/design:**

An open-label, randomized, controlled, parallel-group, multicenter trial in lung transplant recipients will be conducted to investigate the safety and efficacy of immunosuppression guided by TTV monitoring as an add-on to conventional therapeutic drug monitoring. Adult lung transplant recipients 21 to 42 days after transplantation are eligible to participate. Patients (*N* = 144) will be randomized 1:1 to the experimental intervention (arm 1: immunosuppression guided by TTV monitoring in addition to conventional therapeutic drug monitoring of tacrolimus trough levels) and control intervention (arm 2: conventional therapeutic drug monitoring). Outcomes will be assessed 12 months after randomization with the change in glomerular filtration rate as the primary endpoint. Secondary endpoints will be additional measurements of renal function, allograft function, incidence of acute rejections, incidence of chronic lung allograft dysfunction, graft loss, and infections.

**Discussion:**

The results of this randomized controlled trial may reduce the toxicity of immunosuppression after lung transplantation while maintaining the efficacy of immunosuppression. Study results are transferable to all other solid organ transplantations.

**Trial registration:**

ClinicalTrials.gov NCT04198506. Registered on 12 December 2019

## Background

High-dose immunosuppression containing calcineurin inhibitors (CNI) is essential after lung transplantation. Dosing is usually guided by fixed target levels, established to keep the balance between over-dose causing toxicity and increased risk of infections or under-dose with a risk of graft injury.

Therapeutic drug monitoring represents the current gold standard of guiding immunosuppression after solid organ transplantation [1]. Despite rigorous monitoring, acute rejection occurs in approximately one third of patients in the first year after lung transplantation [2]. Immunosuppressive regimens are responsible for considerable toxicity. Approximately 24% of the recipients will develop kidney failure within 1 year of transplantation and 2% end-stage kidney disease. Increased infection rates are associated with over-immunosuppression, and infections are the leading cause of death during the first postoperative year.

Clinical experience suggests that individual tailoring of immunosuppression could potentially optimize patient outcome [3–6]. Reliable, reproducible, cost-effective, and non-invasive biomarkers are needed to reduce the risk of graft injury and toxicity to guide immunosuppression.

Latent DNA viruses in the whole blood (e.g., torque teno virus (TTV)) are detectable in the vast majority of lung transplant recipients [3].The load of these latent viruses was associated with the strength of immunosuppression in solid organ recipients [7].

DNA viruses in the whole blood (torque teno virus/TTV, HHV-6, EBV) and urine (BK virus) can be detected in the majority of humans including transplant recipients. Some of them do not cause symptoms of infection, for example, TTV. The viral load of TTV was used as a surrogate biomarker of cell-mediated immunity (load increasing with the strength of immunosuppression) but has never been studied in a prospective trial. It is suggested by pivotal studies [3] that CNI-based immunosuppression may be reduced in the majority of lung transplant recipients during the first postoperative year.

Guiding immunosuppression by an immune response assay in a prospective trial resulted in reductions in CNI doses of 13–25% within the first year after liver transplantation, with documented reductions in bacterial and fungal infections [6]. In lung transplant recipients, a CNI reduction of 50% has led to an improvement of GFR (CKD-EPI) by 10 ml/min/1.73 m^2^ after 12 months in a recent randomized trial [8]. With the management of trough levels by TTV load, it is expected that a similar CNI dose reduction can be achieved.

The results of the VIGILung trial may have an impact on therapeutic strategies for patients after lung transplantation. Study results may be transferable to all other solid organ transplantations.

## Methods/design

### Objectives

The aim of this randomized controlled trial is the prospective investigation of the safety and efficacy of an individual adaptation of the tacrolimus-based immunosuppression by a non-invasive biomarker (torque teno virus (TTV) load in the whole blood).

The primary endpoint will be Δ-glomerular filtration rate (GFR) defined as the change of the glomerular filtration rate GFR between randomization and 12 months thereafter as an indicator for toxicity. GFR will be estimated using the Chronic Kidney Disease Epidemiology Collaboration (CKD-EPI) formula [9].

Secondary outcomes include further parameters on renal function, parameters regarding lung allograft function forced expiratory volume in 1 s (FEV1) in % of baseline, incidence of acute rejections, lymphocytic bronchiolitis and/or chronic lung allograft dysfunction, re-transplantation or death due to graft failure, infections (cytomegalovirus (CMV), community-acquired respiratory viruses (CARV), fungal or bacterial infections), incidence of unscheduled emergency hospitalizations or admissions for intensive care unit (ICU), Quality of Life Questionnaire (EQ-5D) and exercise capacity, the state of immune-system (cluster of differentiation 4 (CD4)-lymphocytes, donor-specific antibodies (DSA), IgG level and use of rescue immune therapy), and details on the tacrolimus immunosuppression (tacrolimus trough levels, tacrolimus doses, and number of adjustment of immunosuppression).

## Design and participants

The screening of the patients will be performed in two participating study sites (Hannover Medical School and University of Vienna). We assume that screening of 250 patients will result in 144 subjects eligible for the study. The recruitment period is expected to be 39 months.

Selected in- and exclusion criteria are as follows:

Inclusion criteria:
Adult patients 21 to 42 days after de novo lung transplantation (bilateral or combined)Tacrolimus based immunosuppressionDetectable TTV load at randomization (> 2.7 log 10 copies/mL)Women of child-bearing potential: negative serum pregnancy test and highly effective methods of contraception throughout the study.

Exclusion criteria:
History or high-risk of obstructive airway complications after lung transplantationRespiratory failure (need for oxygen therapy or ventilation at screening) inability to undergo transbronchial biopsyAdvanced kidney failure (GFR CKD-EPI < 30 ml/min/1.73 m^2^ at inclusion and/or current renal replacement therapy at inclusion or randomizationAdvanced liver cirrhosis (CHILD-Pugh Score C) after lung transplantationFluctuating tacrolimus drug levels (less than 20% in target range after transplantation)Symptoms of significant mental illness with the inability to cooperate or communicate with the investigatorUnlikeliness to comply with the study requirementsHIV positivity

### Randomization

Randomization will be performed centrally via telefax by the Center for Clinical Trials (KKS) of the Philipps-University Marburg for patients matching all eligibility criteria and will be stratified by high-risk CMV status (D+R−) (yes/no) and center using randomization lists generated at KKS with permuted blocks of randomly varying size. The chance for allocation to the control and experimental group is 1:1. Investigators at the participating sites request the randomization result by faxing the completed randomization form, whereupon KKS staff will consult the randomization database and transmit the result to the investigator.

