**Fig. 1 Fig1:**
[figure not shown]
Trial flow chart and treatment groups

Study visits will be performed at months 1, 2, and 3 after transplantation and at months 3, 6, 9, and 12 after randomization. The final examination will be performed at month 12 after randomization or in case of a premature end of study treatment.

In both treatment arms, during maintenance, immunosuppression interruption of one out of three immunosuppressive components for up to 4 weeks will be allowed, e.g., in case of cell cycle inhibitors induce severe toxicity (e.g., leukopenia < 4000/μl, thrombocytopenia < 50,000/μl, anemia with hemoglobin < 8 g/dl).

After transplantation, tacrolimus and additional immunosuppressive drugs, usually a cell cycle inhibitor (mycophenolate mofetil, mycophenolate sodium, azathioprine) and prednisolone, are given.

In case of induction therapy with alemtuzumab, tacrolimus and prednisolone are given from day 0 and cell cycle inhibitors are delayed until the restoration of lymphocyte count—usually after 12 months [5, 10].

Adjustment of tacrolimus immunosuppression will be established in predefined steps, derived from previous trials in immunosuppression [11]. Immunosuppression (IS) will be managed according to predefined steps (with gradually reduced tacrolimus target levels from step 8 to 1. Patients without induction with alemtuzumab will start on step 6 (target trough level of tacrolimus 8–12 ng/ml), and patients with induction with alemtuzumab will start on step 4 (target trough level of tacrolimus 6–10 ng/ml) in this scheme. Trough levels of tacrolimus will be determined according to liquid chromatography coupled with mass spectrometry (LC-MS) at least once a month.

All patients who experience an acute cellular rejection after reduction of CNI will be put on increased doses of calcineurin inhibitors.

In arm II, the tacrolimus-based immunosuppression will be guided by conventional therapeutic drug monitoring (TDM). In patients randomized to the conventional CNI dosing, the immunosuppressive drugs should be applied according to trough levels, signs of toxicity, and center practice.

In arm I, the immunosuppression will be guided by the torque teno virus (TTV) monitoring and conventional therapeutic drug monitoring (TDM) (Fig. 2). Reduction in target trough levels will only be performed in stable patients after exclusion of silent rejection in the transbronchial biopsy.

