#### Primary efficacy analysis

The primary efficacy endpoint ΔGFR is defined as the change of the glomerular filtration rate GFR between randomization and 12 months thereafter. GFR will be estimated using the CKD-EPI formula. The primary endpoint analysis will be adjusted for randomization strata and baseline. No subgroup analyses are planned.

An analysis of covariance (ANCOVA) with strata used at randomization and treatment as fixed factors, and the baseline GFR as a covariate is used to test for a difference in location of ΔGFR (in ml/min/1.73 m^2^) between the groups (two-sided at a 0.05 significance level). The analysis of the primary endpoint will be based on the intention-to-treat population.

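### Alemtuzumab induction sets the starting tacrolimus target but is absent from the primary ANCOVA, and the mixed models name neither induction nor center: a modest, cheaply recovered loss of precision

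*Protocol article*

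**What the plan says.** All places are in the protocol article.

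- **Design and participants.** The selected eligibility criteria require tacrolimus treatment and place no restriction on induction. There are two sites.
- **Randomization.** Allocation is "stratified by high-risk CMV status (D+R−) (yes/no) and center using randomization lists".
- **Follow-up protocol.** The step scheme differs by induction: "Patients without induction with alemtuzumab will start on step 6 (target trough level of tacrolimus 8–12 ng/ml"), whereas "patients with induction with alemtuzumab will start on step 4 (target trough level of tacrolimus 6–10 ng/ml) in this scheme". Induced patients begin on tacrolimus and prednisolone, and "cell cycle inhibitors are delayed until the restoration of lymphocyte count—usually after 12 months".
- **Primary efficacy analysis.** The model is fixed as "An analysis of covariance (ANCOVA) with strata used at randomization and treatment as fixed factors, and the baseline GFR as a covariate". The section adds: "No subgroup analyses are planned".
- **Secondary endpoints.** The covariates named for the mixed models are group, high-risk CMV status, time and the group-by-time interaction. Center and induction are not named. Further detail is deferred to the statistical analysis plan.

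**The concern.** The trial's premise, set out in the Background, is that lower calcineurin inhibitor exposure preserves GFR. Induction fixes the starting value of the quantity the intervention manipulates, so it is a plausible predictor of ΔGFR and a near-certain predictor of tacrolimus trough and dose.

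It also determines whether a patient is on two or three drugs. Randomization takes place at visit 3, about three months after transplantation. The usual delay of the cell cycle inhibitor therefore covers roughly 12 − 3 = 9 of the 12 months of follow-up. The CD4 counts at 0 and 6 months after randomization fall inside that window.

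The Discussion justifies CMV status as a stratum by its link with TTV load. Induction, which acts on the tacrolimus target directly, has a comparable claim to a place in the models. At stake are the precision of the treatment contrast and its exposure to a chance imbalance in induction, in the primary analysis and more plainly in the repeated-measures analyses of trough, dose and CD4.

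**Working it through.** **1. The plan's own figure.** Inputs from Sample size calculation: difference 10, SD 20, two-sided 5%, power 80%, dropout 10%. The two-sample t test (noncentral t) gives power 79.5% at 63 per arm and 80.1% at 64, so 64 per arm is reproduced. 64/0.9 = 71.1, rounded up to 72 per arm, or 144. The sample size is not in question.

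**2. Assumed inputs.** The article states neither the induced share *p* nor the effect *g* of induction on mean ΔGFR. I take *p* = 10% to 50% and *g* = 5 to 15 ml/min/1.73 m².

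**3. Precision.** Holding the total SD at 20, induction explains R² = p(1−p)g²/400, and the residual SD after adjustment is 20·√(1−R²). Power at 64 per arm for a difference of 10, ignoring the one degree of freedom spent:

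| p | g | R² | Residual SD | Power |
|---|---|---|---|---|
| not adjusted | – | – | 20 | 80.1% |
| 10% | 5 | 0.6% | 19.94 | 80.4% |
| 30% | 5 | 1.3% | 19.87 | 80.7% |
| 30% | 10 | 5.3% | 19.47 | 82.2% |
| 50% | 10 | 6.3% | 19.36 | 82.6% |
| 50% | 15 | 14.1% | 18.54 | 85.7% |

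**4. Chance imbalance.** With 72 per arm and no link between induction and the strata, the difference between arms in the induced share has SD √(2p(1−p)/72).

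| p | SD (points) | 95% limit (points) | P(imbalance ≥ 10 points) |
|---|---|---|---|
| 10% | 5.0 | 9.8 | 3.7% |
| 20% | 6.7 | 13.1 | 11.7% |
| 30% | 7.6 | 15.0 | 17.2% |
| 50% | 8.3 | 16.3 | 21.1% |

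At the 95% limit, across these shares, the unadjusted treatment difference moves by limit × g: 0.5–0.8 (g = 5), 1.0–1.6 (g = 10) or 1.5–2.5 (g = 15). The target difference is 10, and its standard error is 20·√(2/64) = 3.5.

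**5. Validity.** A simulation used 4,000 runs per scenario, 128 patients in two equal centers, blocks of 4 within center and CMV status, 25% CMV high-risk, p = 50%, g = 10 and no baseline GFR term (all assumptions). Type I error was 5.3% with induction omitted and 5.3% with it included. The mean estimate was 10.05 in both models for a true difference of 10. Power was 80.2% omitted and 82.7% included.

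**6. What center absorbs.** With 20% induced at one center and 80% at the other, the variance of induction within centers is 0.2 × 0.8 = 0.16, against 0.25 overall. The center term then already carries 0.09/0.25 = 36% of what adjustment could remove. In simulation the gain shrank to 80.9% versus 82.6%. With complete separation the two factors are collinear and there is nothing further to gain.

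**7. Tacrolimus outcomes.** The midpoints of the starting targets are (8+12)/2 = 10 and (6+10)/2 = 8 ng/ml, a gap of 2, though the ranges overlap from 8 to 10. If that gap persisted, an imbalance of 9.8 to 16.3 points would shift the mean trough contrast by 0.20 to 0.33 ng/ml.

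**The case against.** The strongest reply is that nothing here is wrong. Adjusting for the randomization strata and the baseline value is a standard, valid, pre-specified model, and chance imbalance is already reflected in the confidence interval. That stands.

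The size of the effect is also assumed. The Background cites a 50% calcineurin inhibitor reduction that gave 10 ml/min/1.73 m². Scaling that linearly to the 20% gap in target midpoints (2/10) gives 10 × 20/50 = 4, below the lowest *g* used above. At p = 50% this explains 0.25 × 16/400 = 1.0% of variance, and power would be about 80.5%. Baseline GFR, measured after some months on different targets, may absorb part of the effect too. This also stands, and it makes the lower end of the power range more plausible than the upper for the primary endpoint.

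A third reply is that center, at two sites, already carries induction. It may do so in the primary model, but the article does not report induction use by site. In the mixed models the reply fails, because center is not among the named covariates.

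A fourth is that this belongs to the analysis plan. Full details are indeed deferred there, and that document is not at hand. However, the article states the ANCOVA terms and names the mixed-model covariates, so these are choices made rather than details left open.

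A reader might also infer that induced patients have less room to step down, so that the treatment effect differs by induction. That would be effect modification, which a main-effect term does not address. The documents give no evidence on its size.

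**Conclusion.** The point holds as a question of efficiency. A baseline variable that the trial must already know, because it sets the starting step, is missing from models whose terms the article states. Under the assumed shares and effects, power rises from 80.1% to 80.4–85.7%. The gain in the primary model is smaller the more induction follows center, and nil if the two coincide. The gap is clearest in the mixed models for trough, dose and CD4, where no center term stands in for induction.

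A reader might go further and conclude that the primary result will be biased, that type I error is inflated, that the trial is underpowered or that the randomization is defective. None of these is supported. Induction precedes randomization, simulated type I error is 5.3% either way, the planned 64 per arm is reproduced without any induction term, and allocation by CMV status and center is valid as it stands.

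**What to change.** Before database lock, state in the statistical analysis plan:

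- Induction (yes/no) is a fixed factor in the primary ANCOVA.
- Induction and center are fixed factors in the secondary mixed models, above all for tacrolimus trough, daily dose and CD4 count.
- Induction is shown by arm and by center in the baseline table.
- If induction coincides with center, center alone is kept in both sets of models, and the reason is given.

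The rule for the last case should not depend on treatment results, so it is best settled from the induction-by-center counts alone. Adding the factor after results are seen would look data-driven. The cost is a few lines of text and one degree of freedom per added term. Recruitment has begun, and the randomization lists and the 144 patients need no change.

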### Trial intervention and control

After lung transplantation (day 0), all patients will receive a standard tacrolimus-based triple immunosuppressive regime (tacrolimus, prednisolone, and a cell cycle inhibitor (depending on induction therapy with alemtuzumab)). Tacrolimus-based immunosuppressive protocols represent the standard of care worldwide [2] and were therefore chosen as the comparator. Inclusion and screening will occur 21 to 42 days after lung transplantation; a further screening visit will occur 4 weeks later, especially to evaluate the achievement of a sufficient TTV level.

### Follow-up protocol

At visit 3 patients will be assigned to one of the two treatment groups detailed in Fig. 1.

**Fig. 1 Fig1:**
[figure not shown]
Trial flow chart and treatment groups

Study visits will be performed at months 1, 2, and 3 after transplantation and at months 3, 6, 9, and 12 after randomization. The final examination will be performed at month 12 after randomization or in case of a premature end of study treatment.

In both treatment arms, during maintenance, immunosuppression interruption of one out of three immunosuppressive components for up to 4 weeks will be allowed, e.g., in case of cell cycle inhibitors induce severe toxicity (e.g., leukopenia < 4000/μl, thrombocytopenia < 50,000/μl, anemia with hemoglobin < 8 g/dl).

After transplantation, tacrolimus and additional immunosuppressive drugs, usually a cell cycle inhibitor (mycophenolate mofetil, mycophenolate sodium, azathioprine) and prednisolone, are given.

In case of induction therapy with alemtuzumab, tacrolimus and prednisolone are given from day 0 and cell cycle inhibitors are delayed until the restoration of lymphocyte count—usually after 12 months [5, 10].

Adjustment of tacrolimus immunosuppression will be established in predefined steps, derived from previous trials in immunosuppression [11]. Immunosuppression (IS) will be managed according to predefined steps (with gradually reduced tacrolimus target levels from step 8 to 1. Patients without induction with alemtuzumab will start on step 6 (target trough level of tacrolimus 8–12 ng/ml), and patients with induction with alemtuzumab will start on step 4 (target trough level of tacrolimus 6–10 ng/ml) in this scheme. Trough levels of tacrolimus will be determined according to liquid chromatography coupled with mass spectrometry (LC-MS) at least once a month.

All patients who experience an acute cellular rejection after reduction of CNI will be put on increased doses of calcineurin inhibitors.

In arm II, the tacrolimus-based immunosuppression will be guided by conventional therapeutic drug monitoring (TDM). In patients randomized to the conventional CNI dosing, the immunosuppressive drugs should be applied according to trough levels, signs of toxicity, and center practice.

In arm I, the immunosuppression will be guided by the torque teno virus (TTV) monitoring and conventional therapeutic drug monitoring (TDM) (Fig. 2). Reduction in target trough levels will only be performed in stable patients after exclusion of silent rejection in the transbronchial biopsy.

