#### Sample size calculation

The sample size calculation is performed assuming a *t* test of ΔGFR. Because adjusting for stratification factors is assumed to reduce variability, the power for the ANCOVA test of the treatment variable is expected to be rather higher than lower compared to the *t* test.

The sample size calculation is based on the assumption of a mean decline in GFR of 15 between randomization and 12 months thereafter and a standard deviation of 20 in the control group. Two randomized trials [8, 13] observed effect sizes of a similar magnitude. Compared to the control group, a mean decline in GFR of 5 in the experimental group (i.e., difference of 10 in GFR declines between the intervention groups) is regarded as clinically relevant. For a 2-sided significance level of 5% and a power of 80%, 64 patients per group (*n* = 128 in total) are needed to achieve a power of 80% if the true difference in means is 10 and the standard deviation is 20 in both. With an estimated dropout rate of 10%, 144 patients have to be randomized.

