#### Data collection

Patient data are collected during the planned study visits on site using electronic case report forms (e-CRF) hosted by KKS Marburg. The data are entered directly at the participating sites via a web browser to the e-CRF and are transferred via TLS encryption to the central database.

Access to the e-CRF is only allowed for documented trial personnel using individual user accounts.

In a multistage procedure, the given data will be checked electronically for their plausibility and consistency. Even during data collection, implausible data will be flagged automatically by implemented validation checks. In the next stage, detected inconsistencies and missing or implausible data will be clarified with queries and necessary changes will be carried out.

In order to ensure the anonymity of the patient data, the patient data in the e-CRF are recorded with a patient number consisting of a center number and a consecutive number. An allocation list (Rando-Log) containing the patient number and the identifying data of the patient is only kept in the participating site.

Missing data will be addressed by intention-to-treat (ITT) analysis by single and multiple imputations, weighted estimating equations or model-based strategies. Specific details on the handling of missing data will be given in a statistical analysis plan that will be finalized prior to database lock.

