All participants will be offered continuous follow-up after completion of the trial in the specialized lung transplant clinics in participating centers and are taken into account by patients in the vast majority. In Europe, lifelong center-based follow-up is the standard of care after lung transplantation to assure optimal patient management, quality management, and handling of post-trial complications. In both centers in case or irreversible graft loss, the possibility of re-do transplantation can be offered.

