The authors recognize that the COVID-19 public health emergency may impact the conduct of the trial, e.g., by site personnel or trial participants become infected with COVID-19, quarantines, site closures, and travel limitations. Safety of trial participants is ensured by the prescription of immunosuppressants by local physicians and remote monitoring of patients by telephone and video consultation [20]. During the first wave of the pandemic, shortage in immunosuppressive medications was not noted in Germany and Austria. In-person visits by indications were still possible in both participating centers. Changes in the study visit schedules, missed visits, or patient discontinuations may lead to missing information. Temporary stopping of recruitment may limit the amount of missing data.

The results of this trial might have a large impact on therapeutic strategies for patients after lung transplantation. Furthermore, this study will contribute to improve evidence-based therapy in these patients. Study results are transferable to all other solid organ transplantations.

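### As written, a patient who ends study treatment early has no trial-scheduled month-12 GFR, although the primary intention-to-treat analysis needs one

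*Protocol article*

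**What the plan says.** All references are to the protocol article.

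- **Follow-up protocol** (text after Fig. 1) sets the schedule: "Study visits will be performed at months 1, 2, and 3 after transplantation and at months 3, 6, 9, and 12 after randomization". The rule at issue is in the next sentence: "The final examination will be performed at month 12 after randomization or in case of a premature end of study treatment".
- **Primary efficacy analysis** defines the endpoint: "The primary efficacy endpoint ΔGFR is defined as the change of the glomerular filtration rate GFR between randomization and 12 months thereafter". It then fixes the population: "The analysis of the primary endpoint will be based on the intention-to-treat population". Outcome assessments likewise requires creatinine at month 12, and counts most clinical secondary outcomes over the 12 months after randomization.
- **Data collection** covers gaps by analysis methods: "Missing data will be addressed by intention-to-treat (ITT) analysis by single and multiple imputations, weighted estimating equations or model-based strategies". It leaves the details to the analysis plan.
- **Discussion**, in the paragraph on COVID-19, expects gaps: "Changes in the study visit schedules, missed visits, or patient discontinuations may lead to missing information".
- **Safety endpoints**, last paragraph, notes that in Europe "lifelong center-based follow-up is the standard of care after lung transplantation". This describes the clinic care offered once the trial is over.

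**The concern.** The early final examination is triggered by the end of study treatment, not by withdrawal of consent or loss to follow-up. It stands as an alternative to month 12, and an examination called final implies none after it. An intention-to-treat comparison needs the outcome whether or not the patient stayed on the assigned strategy. If the patients who leave the strategy also leave the visit schedule, the comparison at month 12 rests on those who stayed, plus assumptions about the rest.

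The consequence is not confined to GFR. Rejection, infection, rescue therapy and chronic lung allograft dysfunction are counted up to month 12. By the definition in the Discussion, the last of these needs an FEV1 decline that persists for at least 3 months, so an early exit can prevent its confirmation. The trial expects lower tacrolimus exposure in the experimental arm, so shortened follow-up could weaken the evidence that efficacy is maintained.

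**Working it through.** **1. The passages side by side.** Take a patient whose study treatment ends at month 4. Under the Follow-up protocol section the final examination falls at month 4. The primary endpoint needs creatinine at month 12. No section continues the month 6, 9 and 12 visits for this patient or asks for a later creatinine. Data collection handles a missing value; it does not obtain one. That the value is not collected is thus an inference from the word final and from the absence of a continuation rule. The article does not say so outright.

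**2. The plan's own figure.** Inputs from Sample size calculation: decline 15 in controls, 5 in the experimental arm, SD 20, and "For a 2-sided significance level of 5% and a power of 80%, 64 patients per group".
- Standardized difference = 10/20 = 0.5. The two-sample t test gives 63.77, so 64 per group (power 80.1%).
- 10% dropout: 64/0.9 = 71.1, so 72 per arm and 144 in total.

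The stated figures reproduce. The problem is one of data collection, not arithmetic.

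**3. Power** for a true difference of 10 with 144 randomized:

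| Without a month-12 value | Patients analysed | Power |
|---|---|---|
| 0% | 144 | 84.6% |
| 10% | 129.6 | 80.6% |
| 20% | 115.2 | 75.8% |

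The 10% allowance covers a loss of power of that size. It does not address bias.

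**4. Bias, formula.** Let p be the share of an arm that stops and g the extra 12-month decline of stoppers over completers, with subscripts E (experimental) and C (control). Suppose completers decline by 5 and 15. Then

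difference among all randomized = (15 + p_C·g_C) − (5 + p_E·g_E) = 10 − (p_E·g_E − p_C·g_C),

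while completers show 10. The article gives no p or g, so every value below is an assumption.

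**5. Experimental stoppers decline like controls, control stoppers like other controls** (g_E = 15 − 5 = 10, g_C = 0):
- p_E = 10%: 10 − 0.10 × 10 = 9.0
- p_E = 20%: 10 − 0.20 × 10 = 8.0

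Completers overstate the difference by 1.0–2.0. The standard error with 72 per arm is 20 × √(2/72) = 3.33, so this is 0.30–0.60 standard errors.

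**6. Opposite direction.** If experimental stoppers do not decline at all (g_E = 0 − 5 = −5), 10% stopping gives 10 + 0.5 = 10.5, and completers understate the difference.

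**7. Cancellation.** The bias is zero when p_E·g_E = p_C·g_C, for instance when share and excess decline are the same in both arms.

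**8. Using the exit GFR as the month-12 value.** Assume linear decline, stopping at month 3, and the control slope afterwards. Carried-forward declines are 5 × 3/12 = 1.25 (experimental) and 15 × 3/12 = 3.75 (control). True declines of stoppers are 1.25 + 15 × 9/12 = 12.5 and 15.
- 20% experimental, 5% control: estimate = (0.95 × 15 + 0.05 × 3.75) − (0.80 × 5 + 0.20 × 1.25) = 14.44 − 4.25 = 10.2. Truth = 15 − (0.80 × 5 + 0.20 × 12.5) = 8.5.
- 10% in each arm: estimate = 13.875 − 4.625 = 9.25. Truth = 15 − 5.75 = 9.25. No bias, because each stopper's decline is understated by 11.25 in both arms.

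**The case against.** The strongest reply is that the sentence says when a final examination takes place and does not forbid later data. Figs. 1 and 3 and the full protocol, where withdrawal and follow-up rules usually sit, are not shown. That stands and limits confidence. It does not remove the point: the article itself fixes a collection rule, and that rule as worded is at odds with the month-12 endpoint.

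Four stronger readings are tempting, and the article does not support them.

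- *Patients stop because of rejection or toxicity, so the missing values are informative.* No reasons for stopping are given. The Follow-up protocol section deals with rejection, toxicity and temporary interruption of one drug by adjustment within the trial. What counts as a premature end of study treatment is not defined for a monitoring strategy in which both arms receive tacrolimus. The group may be very small.
- *About 14 of 144 patients are affected, because 10% dropout is planned.* That rate is not split by cause. It may include death, withdrawn consent and loss to follow-up, and it is not a rate of stopping treatment.
- *The analysis is intention-to-treat in name only.* The article commits to that population and to handling missing data. The weakness lies in what is collected.
- *Listing single imputation inflates the type I error.* It is one option among several, none is chosen, and the details are deferred to the analysis plan. This is no finding.

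**Conclusion.** The point holds as a gap between the collection rule and the endpoint: as written, patients who end study treatment early have no trial-scheduled month-12 GFR. It should be fixed; confidence is moderate. The size and direction of bias cannot be determined from the article. The illustration of 9.0–8.0 against 10 rests on assumed one-sided stopping of 10–20% with control-like decline afterwards. Other assumptions reverse the bias or make it cancel. What can be said firmly is that the 10% dropout allowance protects power only, and that without month-12 values in stoppers no analysis could show which of these cases applies.

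**What to change.** In the Follow-up protocol section, separate the end of study treatment from the end of study participation. State that:

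- ending study treatment does not end follow-up, and all randomized patients stay on the visit schedule to month 12 unless consent is withdrawn;
- the minimum for every patient is a month-12 serum creatinine, which may come from routine centre follow-up, plus the 12-month rejection, chronic lung allograft dysfunction, graft and vital status outcomes;
- a GFR from an early final examination is not used as the month-12 value.

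The cost is a short amendment and, for the patients concerned, retrieval of routine values or a visit. With two centres and routine long-term clinic follow-up this looks feasible, although the article describes that follow-up as care after the trial and not as trial data, so access to the values has to be provided for. If stoppers do worse, the difference to be detected is smaller: with all 72 per arm observed, power is 76.5% for a difference of 9.0 and 66.4% for 8.0. That would be the actual power of the intention-to-treat comparison in those cases, and is no reason to leave the values uncollected.
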